### 4.4.11 Study profile: sub study three

Figure 6

Masindi District

Kiryandongo District

Districts

HCs

16 Health Centres (VI, III & II)

Control Arm:

8 HCs (n=**868**):

Intervention Arm

8 HCs (n=**868**):

Study Arms

Recruitment & follow-up

**4 months**

Primary Outcomes

Outcome measures among study participants:

1. Timely ANC return visits
2. Completed 4 visits
3. Institutional deliveries
4. Homecare newborn care practices
5. Immunisation status of the newborn

868 Participants per arm Total = **1,736**

Follow-up

**10 months**

# 5.0 Ethical issues and considerations

Clearance will be obtained from the Institutional Review Board of MakSPH and the National Council of Science and Technology in Uganda. Authorisation to perform this research in the two districts will be obtained from both the national Ministry of Health and the district authorities and health managers. Details and benefits of this survey will be presented to the district authorities in a half-day seminar. Informed written consent will be obtained from the health workers and other participating community members (lactating women, TBAs, elderly care givers). Assent will be obtained from senior members of a household in case participants are less than 18 years. Confidentiality will be maintained personal identifications will be stored and only accessed by the study team.

Details of the study will be explained to all participants and they will be informed to feel free to participate or not in the study with no undesirable consequences to them.

# 5.1 Study limitations

1. This study focuses on prenatal mothers attending ANC services at the primary healthcare centres; systematically excluding the 5-10% of pregnant women who may not make any prenatal contact with the health facilities during the current pregnancy.
2. Some pregnant women make first ANC visit late in the third trimester, the primary target for this study are pregnant women reporting with gestation age of up to 28 weeks. For limitations one and two different intervention strategies are required to target this category of pregnant women who may have their peculiar needs different from the ones targeted by this study.
3. The risk of contamination across the study arms -this will be minimised by purposively allocating health centres in the extremes of the districts to either of the two arms.

| Data analysis, Manuscripts for Sub studies one & two |  | May 2012 | September 2012 |
| Sub Study Three | Not yet Started | Expected to begin July 2012 | To End Oct 2013 |
| Data analysis and manuscripts for Sub study three |  | Expected to begin December 2012 | To End January 2014 |
| Dissertation writing and submission of thesis |  | March 2014 | July 2014 |
| Defence |  |  | November 2014 |

## ****Annex**** ****1**** Knowledge and perception of PHC workers

Adapted from ([Leif E, Nguyen T et al. 2009](#_ENREF_53)) for sub study one

**Optimization of individual prenatal education offered to pregnant women in Masindi and Kiryandongo district, Western Uganda: A community Intervention trial**

**Cadre of health worker**

1. Nurse Assistant,
2. Nurse,
3. Midwife circle appropriately

**Which level of healthcare are you currently working in?**

1. Hospital
2. HC IV
3. HC III

Which department are you currently deployed in?

1. Maternity, **2.** ANC, **3**. FP
2. Children, **5.** Male, **6**. Female, **7**. OPD

**Prenatal care:**

1. **Is it important for a pregnant woman to attend Antenatal care clinics at the health facility?**
2. Yes,
3. No,
4. I have not opinion,
5. **When should a woman make the first antenatal care visit during pregnancy?**
6. Immediately she misses her menstrual period,
7. After she has missed her period for two consecutive months,
8. After three months, d) Any time she wishes,
9. I have no opinion
10. **Who do you think should offer Antenatal care services to pregnant women? (*circle as many as you think)***
11. A midwife,
12. A Nurse,
13. A medical Doctor,
14. TBA,
15. Relative,
16. I have no opinion
17. **How many times should a pregnant woman attend antenatal care during the entire period of the pregnancy?**
18. At least once,
19. At least two times,
20. At least three times,
21. At least four times,
22. Any number of times she wishes,
23. I have no opinion
24. **What are the recommended routine interventions during antenatal clinics? (*circle all possible answers)***
25. History taking,
26. Physical examinations,
27. Laboratory examinations,
28. Health education,
29. Assessment for referral,
30. I have no opinion,
31. Routine prophylaxis
32. **Do you think you should provide health education to a pregnant woman every time she visits the antenatal clinic?**
33. No, only once in the first visit,
34. No, only once in the last visit,
35. Yes only once during the entire pregnancy
36. Yes for each visit,
37. Not necessary to give health education at all,
38. I have no opinion
39. **What are some of the vital information during pregnancy that you can discuss with a pregnant woman? (*circle all those you think are appropriate*)**
40. Dangers and complications during pregnancy,
41. Birth preparation,
42. Caring for the newborn baby,
43. The advantages of delivering in the health facility,
44. I have no opinion

1. **When a pregnant woman makes her first visit to the ANC clinic what are some of the important danger signs related to pregnancy that you will explain to her? (*circle as many as you think)***
2. Swelling of the feet and face,
3. Excessive vomiting,
4. Increased appetite for food,
5. I have no opinion
6. **What are some of the parameters that you will routinely measure during all prenatal visits? (*circle as many as you think*)**
7. Weight,
8. Blood Pressure,
9. Height of fundus,
10. I have no opinion

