## ii) Neonatal mortality-the Ugandan perspective

The newborn mortality in Uganda is estimated at 29/1000 live births translating to about 45,000 deaths in the first month of life ([MOH 2010a](#_ENREF_60)). About 82% of these deaths is caused by three conditions: sepsis (32%); birth asphyxia (26%) and; low birth weight (25%); while maternal mortality is estimated to be 435/100,000 live births with major causes of maternal mortality in Uganda identified as haemorrhage (30%), infection (19%), obstructed labour (10%), pregnancy induced hypertension ( 15%) and abortions (16%) ([MOH 2010a](#_ENREF_60)).

Uganda covers an area of 241,000 square kilometres with a population of 32.2 million inhabitants and population density of 133 inhabitants per square kilometre and a rural population of 80%. The total fertility rate is 6.7 annual growth rate of 3.2% per annum and contraceptive prevalence rate of 24%. Under five mortality of 137/1000 live births; infant mortality is 75/1000 live births. About 72% of the population lives within 5km radius from the nearest health facility and 61% of the approved position for the workforce that is filled ([MOH 2010b](#_ENREF_61)) .

The current national health policy document for Uganda ([MOH 2010c](#_ENREF_62)) underscores the roles that promotive and preventive services can play in increasing access to essential services. This policy document further elaborates the need to ensure that people understand their health rights and responsibilities and improve awareness by causing change in attitudes, practices and behaviours. Various national policy documents ([MOH 2010a](#_ENREF_60); [MOH 2010b](#_ENREF_61); [MOH 2010c](#_ENREF_62)) have laid specific emphasis on the continuum of care both across time period (pregnancy-delivery-post-natal) and across various levels of care (community-first referral and second referral level).

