## 4.2.8 Study variables

- Perceptions of health workers about comprehensive maternal and newborn care
  - Provision of technical ANC services for example taking and recording BP, weight, screening for HIV integrated with,
  - Provision of less technical and more promotional services mainly health education
- Perception of health workers about working with Community Health Workers
- Knowledge of health workers about pre-natal care
  - Dietary requirement for pregnant women
  - Danger signs during pregnancy
  - Birth preparation
- Knowledge of health workers about neo-natal care
  - Hygiene and cord care
  - Warmth for the newborn
  - Early initiation and exclusive breast feeding
  - Recognition of danger signs

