## 4.2.10 Data analysis plan

Quantitative data will be analysed and presented as descriptive statistics in terms of proportions of health workers who will obtain a minimum acceptable score; a second part will stratify scores according to the different health cadres for comparison purposes. We will capture the unique health workers’ perspectives towards provision of individual educational interventions for prenatal women by the health workers on the one hand and by CHWs on the other. Meanwhile for the qualitative data contents will be analysed and presented according emerging themes and these will be used to triangulate with the quantitative information gathered.

Results from this study will illuminate knowledge gaps and major implementation challenges with delivering educational and counselling interventions to prenatal women during ANC at the primary care facilities. It will further provide information on alternative ways of engaging community health workers in the provision of educational interventions at the primary care level. And finally it will suggest ways of utilising mobile phones to enhance return prenatal visits, increase institutional deliveries and improve newborn homecare practices.

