**C: Information on Delivery**

1. Mode of delivery of the current baby:

**1**) Spontaneous Vaginal delivery;

**2**) C/S

**3**) vacuum;

4) Forceps

1. Place of delivery:

**1)** health centre,

**2)** hospital

**3)** home

**4**) on the way to Health Facility

**5)** At the TBAs home

1. Who attended to you during delivery

**1**) By trained health worker

**2**) A close relative

**3**) By TBA

**4)** Unattended to

1. Timing of labour-in your view was this labour:

**1)** Normal

**2)** Longer than usual

**3)** Too long

**4)** Too short

**5)** No idea

1. Did you develop any intra-partum complication: *(Circle all that apply)*
2. too long labour
3. bleeding
4. swelling of the feet
5. convulsions
6. ruptured uterus
7. obstructed labour
8. non

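### The only Annex 1 item on danger signs in pregnancy has no option for bleeding or infection and no 'Other', so sub-study one cannot show whether health workers know those signs (minor)

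*Protocol*

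**What the plan says.** Protocol section 4.2.8 lists "Danger signs during pregnancy" among the things health workers should know about prenatal care, beside diet and birth preparation. The survey instrument is Annex 1. Its Prenatal care section holds one item on the subject. It is set at a woman's first antenatal visit, allows several answers, and asks "what are some of the important danger signs related to pregnancy that you will explain to her". The options are "Swelling of the feet and face", "Excessive vomiting", "Increased appetite for food" and a no-opinion choice.

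Section 4.2.10 plans to report "proportions of health workers who will obtain a minimum acceptable score", then scores by cadre, and expects the results to bring out gaps in knowledge. It states neither a key nor a cut-off.

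Section 1.1(ii) gives the main causes of maternal death in Uganda as haemorrhage 30%, infection 19%, abortions 16%, pregnancy-induced hypertension 15% and obstructed labour 10%. Section 1.3 again names haemorrhage and sepsis, with hypertensive disorders, as the documented direct causes.

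**The concern.** A closed-list knowledge item can detect only the gaps its options allow for. Here a respondent who would never mention bleeding or infection to a pregnant woman can still give the best answer the item permits. A respondent who knows both signs has nowhere to record it. The two look identical in the data.

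At stake is what sub-study one can say about a variable it names. A reader of its results would reasonably take the danger-sign item as evidence on danger-sign knowledge in general. It would be evidence on two signs only, and on neither of the two largest causes of maternal death that the protocol itself lists.

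**Working it through.** This is a check of content, with a few counts.

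1. **Number of items.** Annex 1 has 9 items under Prenatal care and 16 in the later sections (breastfeeding 4, immediate postnatal care 3, infection management 3, temperature and low birth weight 3, home visits 3): 9 + 16 = 25. One of the 25 asks for danger signs in pregnancy. One other prenatal item, on information to discuss with the woman, offers dangers and complications as a topic but names no sign.

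2. **Options against the protocol's causes of death.**

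| Cause (section 1.1(ii)) | Share | Matching option in the item |
|---|---|---|
| Haemorrhage | 30% | none |
| Infection | 19% | none |
| Abortions | 16% | none |
| Pregnancy-induced hypertension | 15% | swelling of the feet and face |
| Obstructed labour | 10% | none |

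Excessive vomiting matches none of the listed causes. The argument rests on the first two rows. The other shares should not be added to them, for the reason given under the objection.

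3. **What the answers can show.** Three substantive options allow 2 × 2 × 2 = 8 response patterns. None of the 8 distinguishes a worker who knows bleeding or infection signs from one who does not. Under the natural key (the two signs right, appetite wrong), a respondent who circles two of the three at random is fully right in 1 of 3 cases.

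4. **'Other'.** Of the 16 later items, 15 offer it; the exception is the item on preventing bleeding in the newborn. None of the 9 prenatal items does. The format was available but was not used in this section.

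5. **Other sources in sub-study one.** The focus-group and key-informant guides (Annexes 2 and 3) ask which health education messages are given. Their listed probes cover birth preparation, clean delivery, cord, warmth and feeding, not danger signs in pregnancy.

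6. **Survey size, needed only for the cost.** Section 4.2.7: 1.96² × 0.5 × 0.5 / 0.09² = 118.6, stated as 120; 120 × 1.10 = 132. The stated figure is reproduced to within rounding and does not bear on the point.

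**The case against.** Several stronger readings are tempting, and the documents do not support them.

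- **That a worker ignorant of the leading causes of death scores full marks.** The best possible mark would be on one item of about 25. The planned output is an overall minimum score, and no key is stated. One may exist in an analysis plan not shown. Swelling also bears on pregnancy-induced hypertension. What stands is that no key can recover answers the item never collects.
- **That causes making up 75 of the 90 listed percentage points are untested** (30 + 19 + 16 + 10 of 30 + 19 + 16 + 15 + 10). The arithmetic is right but it is a poor yardstick. The shares cover all maternal deaths, whereas the item concerns signs explained at a first antenatal visit. Obstructed labour is an intrapartum event, section 1.3 places 43% of deaths in the first 24 hours post partum, and section 1.1(ii) does not split haemorrhage or infection by timing. The share signalled antenatally cannot be derived.
- **That the flaw passes into the content of the trial's education package.** Section 4.4.1 assigns the messages to the community survey; the health-worker study informs how antenatal services are re-oriented. Section 4.4.6 already commits the promotional team to discussing danger signs.
- **That Annex 6 sets the content Annex 1 should have had**, because it lists bleeding and convulsions. That question, "Did you develop any intra-partum complication", concerns labour. It supplies usable terms but not a standard for this item.

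It is also fair to say that section 4.2.9 provides for two pre-tests with adjustment of the tools, that the interviews are to be triangulated with the survey, and that the lack of 'Other' runs through the whole prenatal section. These mitigate only in part. The interview probes do not name danger signs in pregnancy, and a pre-test gives no assurance that a missing option will be noticed.

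**Conclusion.** The point holds in a narrow form. The single danger-sign item cannot register knowledge of bleeding or infection signs, the protocol's two largest listed causes of maternal death (30% and 19%), so the named variable is not adequately measured and this gap would go unseen in sub-study one.

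Severity is minor: one item of about 25 in a formative, descriptive survey of 132 staff, with no bearing on the trial's primary outcomes, sample size or analysis. The conclusion assumes that the item is used as printed and that the two signs, not the appetite option, are the credited answers. The loss of information on bleeding and infection does not depend on the second assumption.

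**What to change.** Before the two planned pre-tests:

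- Add bleeding and signs of infection to the option list, and convulsions, a term Annex 6 already uses. The protocol names no maternal sign of infection, so the investigators should choose that wording.
- Add one or more further plausible non-danger options, so that circling everything is not close to a correct answer.
- Add 'Other (specify)', as in nearly all the later items.
- State the key for this item, so that its contribution to the minimum acceptable score is fixed before data collection.

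An exact number of decoys, or a rule that subtracts decoys chosen from signs chosen, is a matter of preference and is not needed to repair the item.

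The cost is a few lines in one item, slightly longer completion for 132 staff, and slightly less comparability with the source questionnaire from which Annex 1 was adapted.

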**Breastfeeding**

1. **When is it most appropriate to initiate breastfeeding after birth?**

**a**) Within the first hour,

**b)** 1-6 h after birth,

**c)** 6-12 h,

**d)** More than 12 h after birth,

**e)** I have no opinion,

**f)** Other.

1. **If the mother experiences that she has not enough breast milk during the first few days after delivery, what advice do you give her?**

**a)** To give formula while waiting for milk production to start,

**b)** To breastfeed more frequently,

**c)** To give rice water, herbal fluids or honey water while waiting for milk production to start,

**d)** Advise the mother to ask someone else to breastfeed her baby: for example, a neighbour who has enough breast milk,

**e)** I have no opinion,

**f)** Other.

1. **For how long should a mother continue to exclusively breastfeed her child?**

**a)** 1 month,

**b**) 2 months,

**c)** 4 months,

**d)** 6 months,

**e)** More than 6 months,

**f)** I have no opinion,

**g)** Other.

1. **According to you, after how long should a mother stop breastfeeding her child completely?**

**a)** 6 months,

**b)** 12 months,

**c)** 18 months,

**d)** 24 months,

**e)** More than 2 years,

**f)** I have no opinion,

**g)** Other

**Immediate postnatal care**

1. **Shortly after birth a healthy newborn baby should be able to: cry loud, have a pink colour to the skin, breathe evenly and have a respiratory rate of 40 – 60 breaths per minute. How would you take care of a baby that does not have these signs shortly after birth? (*circle as many as you think)***

**a)** Dry baby with cloth,

**b)** Use bag and face mask to help baby with respiration,

**c)** Suction of nose and mouth if necessary,

**d)** Slapping baby,

**e)** Pour cold water over baby,

**f)** I have no opinion,

**g)** Other.

1. **What can be done to prevent newborn children from bleeding?**

**a)** Breastfeeding the child,

**b)** Not necessary to give any drugs,

**c)** Give Vitamin K,

**d)** Give Vitamin K_1_,

**e)** I have no opinion,

1. **Do you know what dose of Vitamin K_1_ to give to a newborn baby according to recommendations in the National Guidelines?**

**a)** 0.5 mg, **b)** 1 mg, **c)** 2 mg, **d)** 5 mg, **e)** 10 mg,

**f)** I have no opinion, **g)** Other.

**Infection management**

1. **A newborn child can get eye infections after delivery. Which of the following alternatives would you use to prevent this from occurring? (*circle as many as you think*)**

**a)** Do not apply anything,

**b)** Apply breast milk in the babies’ eyes,

**c)** Clean eyes with sterile water,

**d)** Apply eye drops (silver nitrate) after cleaning eyes,

**e)** I have no opinion,

**f)** Other.

1. **Taking care of the umbilical cord of a newborn after delivery is important. Which of the following alternatives would you consider as important? (*circle as many as you think*)**

**a)** Always clean your hands before touching the cord,

**b)** Cut the cord with a clean instrument (for example, a razor blade),

**c)** Use any sharp instrument for cutting the cord,

**d)** After cutting the cord, apply traditional herbs/medicines,

**e)** Always put a bandage around the cord,

**f)** I have no opinion,

**g)** Other.

1. **What approach would you use to handle an umbilical cord that has any of the following signs: bad smell, oozing blood, small rashes around the umbilical area? (*circle as many as you think)***

**a)** Leave to dry,

**b)** Clean with water and soap,

**c)** Clean with iodine solution,

**d)** Apply antibiotic powder,

**e)** Refer to hospital,

**f)** I have no opinion,

**g)** Other.

**Temperature/Low birth weight**

1. **What is, in your opinion, the best way to stabilise the temperature of a newborn baby? (*circle as many as you think*)**

**a)** Bathing the baby in water of appropriate temperature,

**b)** By putting on clothes and cover head,

**c)** Having the baby skin-to-skin with her/his mother,

**d)** Keep the baby in a room with a temperature of 28-30°C,

**e)** Have the baby close to heat (radiator, fire, etc.),

**f)** I have no opinion,

**g)** Other.

1. **What is the definition of low birth weight for newborn child?**

**a)** Weight is less than 3000 grams,

**b)** Weight is less than 2500 grams,

**c)** Weight is less than 1500 grams,

**d)** Weight is less than 1000 grams,

**e**) I have no opinion,

**f)** Other

1. **What alternatives are important when taking care of a low birth weight baby? (*circle as many as possible)***

**a)** Bath the baby often,

**b)** Start breastfeeding early and frequently,

**c)** Keep the child warm,

**d)** Prevent infection from developing,

**e)** I have no opinion,

**f)** Other.

**Home visits**

1. **Why is it important to conduct home visits to mothers and their newborn babies after delivery? (*circle as many as possible*)**

**a)** To ask and examine the mother about her physical and psychological status,

**b)** To ask the mother about the baby’s behaviour (feeding, stools and urination, umbilical cord condition, etc.),

**c)** Examine the baby regarding icterus, (itching) weight, skin, umbilical cord, temperature, etc,

**d)** I have no opinion, **e)** Other

1. **When is the optimal time for health care personal to conduct the first home visit to a mother and her baby after delivery?**

**a)** Not important with home visits,

**b)** During the first 3 days,

**c)** Between day 3 and day 7,

**d)** Between day 8 and day 14,

**e)** I have no opinion,

**f)** Other.

1. **Who should conduct a home visit to a mother and her newborn baby after delivery? (*circle as many as you think)***
2. No one,
3. A village health worker,
4. A nurse,
5. A midwife,
6. A doctor,
7. I have no opinion,
8. Other

**The end,**

Thank you for your time

## Annex 2 Interview guide for FGD for sub study one

***2.1 Prevention and Promotional activities during ANC***-what are the activities that you routinely conduct during antenatal care at the health facility; (here we probe for history taking, physical examinations, laboratory examinations, Ferrous, Albendazole prophylaxis, health education, assessment for referral,

**What vital health education messages** are provided at this stage of pregnancy in addition to other curative services like Tetanus vaccination, test for Syphilis and HIV; explore for any birth preparation messages (clothing, finances, the relative who will be assisting her during labour, in case of emergency delivery); approaches for clean delivery, use of sterile instruments, tying of the cord, application of substance to the cord, ensuring warmth for the baby, initiation of breast feeding, any specific messages regarding warmth, breast feeding and hygiene, pre-lacteal feeding; what advice is given to the mother about care for the mother and the new born baby (in terms of feeding, hygiene, warmth and care for the cord

***2.5 what are the main challenges you face with this process***-What are/is their frustration with the process of providing the comprehensive ANC package - curative as well as preventive and promotional healthcare services to pregnant mothers and newborn babies; explore for the workload, the time needed to provide the necessary information; the challenges with late arrivals of the mothers and the newborns

***2.6 What you think about VHT performing some of these functions***-What is their opinion about sharing the burden of work with VHTs; what can the VHTs do to bridge this gap; which aspects of care do they think CHWs can do better; which aspects of care are the PHC workers are more comfortable with; how can the two separate roles be harmonised;

***2.7 What relationship they advocate for***-What kind of relationship would they want to see between the formal healthcare system and the CHW/VHTs; what they think about separation of roles between PHC workers and the VHTs; would they encourage consultations from VHT members, or referrals from the VHT; how would they like these referral system to function

***2.8 Possible linkage with formal healthcare system***-how do they think linkages can be created; what activities can the formal healthcare system perform together with the VHTs; how can the functions of the VHTs be monitored; how can the VHTs be supported to function better; how can VHTs enhance the uptake and utilisation of the services organised at the formal health system to reduce on the delays at home

***2.9 How telecommunication can enhance this linkage***-Is there any role for telecommunications in enhancing the linkage between the formal healthcare system and the VHTs; can the telephone system be used for consultations with the first-line health services; is this likely to work; can mobile phones be used to provide reminders to pregnant women through the VHTs; what are the challenges this intervention is likely to encounter; are they (the health workers) ready to be consulted by phone

